## Background

In the clinical setting, a large proportion of children with an autism spectrum disorder (ASD) experience anxiety symptoms. Between 11 % and 84 % of all children with an ASD experience some degree of impairing anxiety [1]. More specifically, 21 % of the children with an ASD suffer from subclinical anxiety [2] and approximately 40 % of the children with an ASD meet the criteria of at least one anxiety disorder [3]. Some of the most frequently reported anxiety disorders and symptoms seen in children with an ASD are simple phobias, generalized anxiety disorder, separation anxiety disorder, obsessive-compulsive disorder and social phobia [1].

Moreover, anxiety is an underlying cause of several symptoms of ASD. For example, anxiety underlies or affects the stereotype and rigid behavior [4] and the problems in social functioning [5] that children with an ASD often show. Anxiety also underlies comorbid symptoms of children with an ASD, for example oppositional and aggressive behavior [6] and depressive symptoms [7]. Furthermore, anxiety in children with an ASD has a negative impact on adaptive functioning, daily living skills and relationships with peers, teachers and family [8–10]. Therefore, it is important that anxiety in children with an ASD is treated and prevented from further escalation.

Recognition of anxiety symptoms in children with an ASD is not new. In the original description of children with an ASD, Kanner [11] stated that a number of these children had “substantial anxiety problems”. Yet, the evaluation and treatment of anxiety in children with an ASD has only recently received empirical attention [1]. Many studies showed the effectiveness of adapted versions of cognitive behavioral therapy (CBT; *e.g.* [12]) or new interventions especially developed for children with an ASD (*e.g.* [13]), reasoning that the traditional form of CBT is not suitable for children with an ASD. On the other hand, a recent study of Van Steensel and Bögels [14] has shown that CBT is effective in reducing anxiety symptoms in children with an ASD, and that CBT is as effective for children with an ASD as for children without an ASD.

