### Design

The present study involves a randomized controlled trial (RCT) with two conditions (experimental versus control), in which it is investigated whether the new video game Mindlight is effective in treating (sub) clinical anxiety symptoms in children with an ASD. For this study, children in the age of 8–16 years old with a diagnosis of an ASD according to the Diagnostic and Statistical Manual of Mental Disorders 4th Edition – Text Revision (DSM-IV-TR; [26]) will be screened for anxiety symptoms. The children with (sub) clinical anxiety symptoms will be selected and approached for participation.

After the selection and recruitment, children will be randomly assigned to the experimental or control condition. At baseline (T0), children, parents and teachers will fill in questionnaires. Moreover, parents will undergo a semi-structured interview (ADIS-P; [27]) to determine whether their child meets the criteria of one or more anxiety disorders. At post-intervention (T1) and at 3-months follow-up (T2), children, parents and teachers will fill in questionnaires again to evaluate the effect of Mindlight. At 3-months follow-up, parents will undergo the semi-structured interview again to test whether Mindlight also had an effect on the present anxiety disorder (s) in the participating children. Fig. 1 shows a schematic overview of the design in the present study.

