### Secondary outcome measures

*Anxiety of the child according to the parents* will be measured with the Dutch translation of the Spence Child Anxiety Scale for Parents (SCAS-P; [29]). The SCAS-P consists of 38 items on a 4-point scale ranging from 0 (never) to 3 (always). The items of the SCAS-P were formulated as closely as possible to the corresponding item of the child version of the SCAS. Only items referring to an internal state (*e.g.* item 4: ‘I feel afraid’) were rephrased into observable behaviour for parents (*e.g.* ‘My child complains of feeling afraid’). The SCAS-P consists of the same six subscales as the child version. The SCAS-P has a good reliability and validity [38].

*The presence of anxiety disorders according to the parents* will be assessed with the Dutch translation of the Anxiety Disorders Interview Schedule for DSM-IV, Parent version (ADIS-P; [27]). This is a semi-structured diagnostic parent interview that can be used to diagnose anxiety disorders in children of 7–17 years old. The interview will be administered by a qualified therapist or by a master student under supervision of a qualified therapist. In this study, the presence of the following DSM-IV anxiety disorders will be examined: separation anxiety disorder, social phobia, specific phobia, panic disorder, agora phobia and generalised anxiety disorder. The interview consists of standardized questions, with ‘yes’, ‘no’ and ‘different’ as possible answers. At the end of the interview, the interviewer has to give his/her clinical judgement about the severity of every disorder. On basis of this judgement, the interviewer will make a definitive decision about the presence (yes/no) of the different anxiety disorders. The ADIS-P has a strong reliability and validity [27].

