### Data analysis/statistical analysis

Following the intention-to-treat principle [48], all children randomized to a condition will be included in the analyses to test the study objectives. Multiple imputations will be used for missing observations at post-intervention and 3-month follow-up. Reporting of the results of the study will be in accordance with the CONSORT 2010 Statement [25].

To investigate the differences in the development of anxiety symptoms between children in the experimental condition and children in the control condition, a 3 (within-subjects: pre, post, follow-up) by 2 (condition: experimental vs. control) ANOVA (repeated measures) will be conducted, with anxiety symptoms (child report) as the dependent variable. The direct effect of Mindlight on parent report of child anxiety, parent/child report of depressive symptoms, and parent/teacher report of social functioning and behavior problems will be investigated in the same way. Furthermore, remission rates of the anxiety disorders that were diagnosed at baseline (with ADIS-P) will be calculated at 3-months follow-up, and Chi-square (*χ*^2^) tests will be conducted to compare remission rates between the experimental and control group. In the above mentioned analysis plan it is assumed that the children will play the game individually and that therefore the data will not be clustered. However, in case of clustered data due to the formation of groups in which several children play the game in the same room, the analyses will be conducted in MPLUS 6.11 [49].

Finally, possible baseline differences between the two conditions in demographic variables (*e.g.* age, sex, educational level), anxiety symptoms, gaming behaviour and treatment expectancies will be checked. Moreover, possible differences in TAU between the experimental and control condition will be checked at all time points. Variables that show different distributions between the two groups will be entered as confounders in all models testing the effectiveness of the intervention.

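### The ADIS-P is tested only as loss of a yes/no diagnosis, although the interview already yields a severity judgement whose baseline-adjusted comparison would have more power

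*Protocol article*

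**What the plan says.** The ADIS-P is given once at T0 and once at T2 (Table 1). The Design section says: "At 3-months follow-up, parents will undergo the semi-structured interview again", in order to "test whether Mindlight also had an effect on the present anxiety disorder (s) in the participating children".

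Under Secondary outcome measures the interview yields two things. First, "the interviewer has to give his/her clinical judgement about the severity of every disorder". Then: "On basis of this judgement, the interviewer will make a definitive decision about the presence (yes/no) of the different anxiety disorders". No severity scale or cut-off is described. On measurement quality the article says only "The ADIS-P has a strong reliability and validity", without a figure.

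The Data analysis section uses only the dichotomy: "remission rates of the anxiety disorders that were diagnosed at baseline (with ADIS-P) will be calculated at 3-months follow-up", followed by chi-square tests between the two arms. Remission is not defined further.

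**The concern.** A graded judgement is collected and then reduced to present or absent for the only ADIS-P test announced. Two children whose severity falls by the same amount count differently if one started just above the diagnostic line and the other well above it. That discards information, in a subset smaller than the 120 randomised because only children diagnosed at T0 can remit.

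There is a second, related effect. Children enter this analysis because one rating put them above the line. If remission is simply a later rating below the same line, some will cross it without any real change. The trial also admits children with subclinical anxiety, so ratings near the line are to be expected.

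At stake is the trial's only diagnostic outcome. A real effect on diagnosed disorders could be missed, and a remission rate quoted for one arm could be taken for recovery.

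**Working it through.** **The plan's own figures.** The article gives no remission rate, ADIS-P reliability or power for this test. Its sample size (86, raised by 40% to 86 × 1.4 = 120.4, so 120) is for the primary outcome and is not affected. Everything below therefore rests on stated assumptions.

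**Inputs**
- From the article: 120 children, 1:1; loss to follow-up 20%; moderate effect f = 0.25. For two groups d = 2f = 0.5, used here as a 0.5 SD fall in severity.
- Assumed, central case: 66% diagnosed at T0. The Background figures of 40% with a disorder and 21% subclinical give 40/(40 + 21) = 0.656. These describe children with ASD in general, not this sample.
- Assumed: normally distributed severity, the same fall in every treated child, and a T0–T2 correlation of 0.6–0.9 (0.4–0.9 in the wider range).

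**Power, central case.** Diagnosed children: 0.66 × 120 = 79; after 20% loss 79 × 0.8 = 63. Simulated power at two-sided 5%:

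| T0–T2 correlation | Chi-square, n = 79 | Adjusted severity, n = 79 | Chi-square, n = 63 | Adjusted severity, n = 63 |
|---|---|---|---|---|
| 0.6 | 49% | 78% | 40% | 67% |
| 0.7 | 52% | 86% | 44% | 78% |
| 0.8 | 56% | 95% | 48% | 89% |
| 0.9 | 68% | >99% | 58% | 99% |

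With no effect, both tests reject in about 5% of trials (4.7–5.8%).

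**Power, wider range.** With 40–85% diagnosed and 20% loss, n runs from 0.40 × 120 × 0.8 = 38 to 0.85 × 120 × 0.8 = 82. With correlation 0.4–0.9, chi-square has about 25–59% power and adjusted severity about 35–99%. The two ranges overlap only across settings. Within each setting severity was ahead, also when the rating was made coarse.

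**Remission by noise alone.** Suppose there is no true change, and remission means no longer rated present.
- With equal margins, P(absent at T2 given present at T0) = (1 − p)(1 − κ), where p is the diagnosed share and κ the agreement of the yes/no decision. At p = 0.80, κ = 0.90: 0.20 × 0.10 = 2%. At p = 0.40, κ = 0.60: 0.60 × 0.40 = 24%.
- With a normal latent severity, a fixed cut c and retest correlation r, the rate is 1 − P(both ratings above c)/p. For r = 0.7, 0.8 and 0.9 it is 31%, 25% and 17% at p = 0.40; 20%, 17% and 12% at p = 0.60; 11%, 9% and 6% at p = 0.80.

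So the rate is roughly 2–30% over this grid. More extreme inputs give 0.5% (p = 0.90, κ = 0.95) to 50% (p = 0.20, r = 0.6).

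**What noise does to the comparison.** Take assumed true remission of 20% against 50%, with 36 per arm: power 77%. If 10% of unremitted children are called remitted, the rates become 20 + 0.8 × 10 = 28% and 50 + 0.5 × 10 = 55%, and power is 65%. At 20% noise they become 36% and 60%, and power is 53%. The contrast shrinks; no false difference is created.

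**Would a stricter remission rule help?** Requiring also a fall of at least 1.96 standard errors of the difference cuts noise remission from 6–31% to 1–4% (p = 0.40–0.80, r = 0.7–0.9). But it also discards true remissions: at reliability 0.8 and n = 63, chi-square power drops from 48% to 25%.

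**The case against.** The strongest reply is that the planned inference is sound. Rates are compared between randomised arms, noise falls on both alike, and type I error stays near 5%. The control arm also plays a game, so no single-arm reading is needed, and the article makes none. All of this stands.

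Loss of diagnosis is a conventional endpoint that clinicians understand. Graded anxiety is already analysed through the SCAS-C (primary) and SCAS-P. ADIS-P remission is not in the abstract's list of secondary outcomes, and the trial is not powered for it. This limits the weight of the point. But the SCAS scales are symptom questionnaires, and the Design section gives the repeat interview its own purpose of testing an effect on diagnosed disorders.

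The article condenses a fuller plan, which may define remission and may use severity. That is why an undefined remission is not itself the finding. The point is the analysis that the article does name.

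The power figures favour severity partly by construction. A continuous normal score, a uniform fall and a correlation of 0.9 produce the values near 99%. At correlations of 0.3–0.5 with 79 children, severity has about 63–71%. The article describes no severity scale, and a child may have several of the six disorders, so a per-child summary must be chosen. These objections narrow the gain without reversing it.

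A reader might go further and infer that some particular share, such as 10–20% or more, of diagnosed children will remit through noise. The documents do not support a figure: they give no reliability and no diagnosed share for this sample. A reader might also infer that the remedy is a minimum fall in severity before remission counts. The last calculation above shows that this would cost further power.

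**Conclusion.** The concern holds as a matter of efficiency and interpretation, not validity. The chi-square comparison is a legitimate test, but it leaves unused a severity judgement that the interview already requires.

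For an assumed 0.5 SD effect with 20% loss, power is about 25–59% for chi-square against about 35–99% for T0-adjusted severity, over 40–85% diagnosed and a T0–T2 correlation of 0.4–0.9. The documents state neither a severity effect, nor the diagnosed share, nor the correlation. The direction is firmer than the size, since severity led in every setting tried.

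If remission is only the loss of the yes/no diagnosis, roughly 2–30% of baseline diagnoses would be lost to rating noise under assumed reliability and prevalence. That share raises both arms' rates and dilutes the contrast. It misleads only someone who reads one arm's rate as recovery. The primary outcome and its sample size are untouched, so this is a worthwhile, inexpensive improvement to a secondary outcome.

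**What to change.** In the Data analysis section:

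- Add, as the main ADIS-P test, a between-arm comparison of the severity judgement at T2 adjusted for its T0 value, among children diagnosed at T0. Use ANCOVA, or an ordinal model if the rating is coarse.
- Fix one summary per child in advance, for example the severity of the disorder that was most severe at baseline. Record its T2 severity even when it is then rated absent.
- Keep diagnosis-free remission and its between-arm difference as a supporting result, and define it.
- State that single-arm remission rates are not to be interpreted as recovery.
- Do not add a minimum-fall requirement to remission.

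The cost is wording, one more analysis, and keeping a value the interviewer already produces. It needs no extra visits or participants. The drawback is that a severity difference is less immediate to clinicians than a remission rate, which will still be reported beside it.

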## Discussion

The present study protocol gives an overview of a study design for a randomized controlled trial testing the effect of the serious game Mindlight in decreasing anxiety symptoms of children with an ASD. The primary aim is to investigate whether Mindlight is effective in reducing (sub) clinical anxiety symptoms of children with an ASD in the age of 8–16 years old. The secondary aims are to investigate whether Mindlight is effective in reducing parent report of child anxiety and the anxiety-related problems in social functioning, depressive symptoms and behavior problems of children with an ASD. It is expected that Mindlight is effective in reducing anxiety symptoms of the children in the experimental condition, compared to the children in the control condition that play Triple Town. Furthermore, it is expected that Mindlight is more effective than Triple Town in reducing parent report of child anxiety, parent/child report of depressive symptoms and parent/teacher report of social functioning and behavior problems.

### Strengths and limitations

The present study design has a few strengths and limitations. A strength is that it is the first study investigating the effect of a serious game in a clinical context with children who are diagnosed with an ASD and who have comorbid (sub) clinical anxiety symptoms, which could lead to a new way of treating anxiety in children with an ASD. An additional strength is that children with an ASD often feel a close affinity for technology and games [24, 15], and that the participating children are probably intrinsically motivated to play a game like Mindlight in therapy. Furthermore, Mindlight includes frequent practice, exposure opportunities, visual aids and structured sensory information, which all stimulate the automatization and the generalization of skills to daily life in the participating children. Another strength is that this study may lead to the implementation of Mindlight in mental health institutes, which may result in an easier access to mental health care, shorter waiting lists and lower therapy costs. Finally, this study has multiple outcome measures, which makes it possible to investigate other direct effects of Mindlight on anxiety-related symptoms (*e.g.* depressive symptoms) of the participating children.

A limitation of the present study design is that the children in the control condition might have played Triple Town already before the start of the study. This may have a positive (*e.g.* more practice) or negative (*r* boredom) influence on the effect of the game. Moreover, only short-term effects (3-months follow-up) of Mindlight will be investigated. In this way, no conclusions can be drawn about the long-term effects of Mindlight on anxiety symptoms of the participating children. Finally, there are no standardized protocols for offering and implementing a video game in a clinical therapy session. This implies that the best form of implementation still needs to be discovered and improved by experience.

### Implications for practice

Anxiety symptoms are highly common in children with an ASD. Still, treatment on anxiety in children with an ASD only recently has received some empirical attention. This may be caused by the fact that anxiety is often underdiagnosed in children with an ASD [1]. In this way, anxiety treatment for children with an ASD is not common and the development of evidence-based anxiety treatments has not been focused upon until recently. By developing and investigating new anxiety treatments for children with an ASD, these may be more frequently offered in mental health institutes in the future. Moreover, if Mindlight turns out to be effective for anxious children with an ASD, it could be considered as a good and suitable therapeutic alternative to the already existing interventions for anxiety in children with an ASD. Mindlight could then be implemented as an evidence-based treatment for children with an ASD in mental health institutes and special education schools.

## Conclusion

This paper aimed to describe a study that will investigate the effect of the serious game Mindlight on (sub) clinical anxiety symptoms of children with an autism spectrum disorder in the age of 8–16 years old. It is expected that children in the experimental condition will show lower levels of anxiety symptoms at 3-months follow-up, compared to children in the control condition. If Mindlight turns out to be effective, this could provide a significant contribution to the evidence-based treatment of anxiety in children with an ASD.
